**Methods/design:**

A parallel groups randomised controlled trial in which smokers who are FDRs of probands with CD are randomly allocated in families to undergo one of two types of assessment of risk for developing CD based on either:

i. DNA analysis, family history of CD and smoking status, or

ii. Family history of CD and smoking status

The primary outcome is stopping smoking for 24 hours or longer in the six months following provision of risk information. The secondary outcomes are seven-day smoking abstinence at one week and six month follow-ups. Randomisation of 470 smoking FDRs of CD probands, with 400 followed up (85%), provides 80% power to detect a difference in the primary outcome of 14% between randomised arms, at the 5% significance level.

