Following receipt of the results booklet, the research counsellor will telephone the participant to administer the brief smoking cessation intervention as previously described.

#### Telephone call 3

A member of the research team who did not deliver the intervention will assess self-reported seven-day smoking cessation approximately one week after telephone call 2 has taken place.

#### Telephone call 4

This will take place six months after the second telephone call to assess the primary endpoint, seven-day smoking cessation, and levels of worry caused by the risk assessment. This telephone call will be made by a member of the research team who did not deliver the intervention and who is blind to allocation. Saliva samples will be collected via post in those who report seven day smoking abstinence, to allow cotinine validation.

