#### Secondary cessation outcomes

##### Seven-day smoking cessation at one week

Self-reported smoking cessation will be assessed at one week following receipt of the CD risk assessment.

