##### Seven-day smoking cessation at six months

At six months abstinence from smoking in the preceding seven days will be assessed using the Russell standard procedures [21], counting participants lost to follow up as being smokers, and self-reported smoking status will be verified biochemically. Validated abstinence requires smoking no more than 5 cigarettes in the prior seven-day period and a cotinine level of <15 ng/ml.

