### Statistical analysis

The analysis of the primary outcome, the proportion of participants reporting having made one or more quit attempts of 24 hours or more in the preceding six months, and the secondary cessation outcomes will be compared between arms by estimating a difference in proportions between arms together with a 95% confidence interval, and the p-value from the associated chi-squared test. The odds ratio and 95% confidence interval will also be reported. Analyses will be on an intention to treat basis with the common assumption for secondary cessation outcomes that all participants are classified as smokers except for those biochemically verified as non-smokers. However, for the primary outcome, those missing this outcome will primarily be treated as missing from the analysis. Missing status will be compared between groups, and the primary difference in proportions will be re-assessed assuming that missing data is imputed as no quit attempt. All tests will be two-sided and assessed at the 5% significance level. Sensitivity analyses will be performed to confirm that clustering makes negligible difference to results and no difference to conclusions or interpretations, using Donner's Method [27]. Hypotheses II and III will be assessed by comparing the primary outcome between mutation status subgroups of the DNA arm with each other and with the control arm. To strengthen the interpretation of these non-randomised comparisons, sensitivity analysis will be undertaken to vary the degree to which mutation status may predict outcome, detailed as part of the statistical analysis plan to be prepared prior to analysis.

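### The smoker-unless-verified rule covers both secondary cessation outcomes, but verification is planned only at six months, so the rule cannot be applied to the one-week outcome

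*Protocol article*

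**What the plan says.** The abstract names two secondary outcomes: "The secondary outcomes are seven-day smoking abstinence at one week and six month follow-ups". The Outcomes section lists both under one heading for secondary cessation outcomes.

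- **One week.** The definition reads "Self-reported smoking cessation will be assessed at one week following receipt of the CD risk assessment". Under Procedure, Telephone call 3, a research team member "will assess self-reported seven-day smoking cessation approximately one week after telephone call 2 has taken place". No sample is mentioned in either place.
- **Six months.** The definition says that "self-reported smoking status will be verified biochemically", gives a cotinine limit of 15 ng/ml, and counts those lost to follow-up as smokers. Under Procedure, Telephone call 4: "Saliva samples will be collected via post in those who report seven day smoking abstinence, to allow cotinine validation".

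The Statistical analysis section then sets one rule for these outcomes together: "the common assumption for secondary cessation outcomes that all participants are classified as smokers except for those biochemically verified as non-smokers". The next sentence makes an exception for the primary outcome only. The same section prescribes, for the primary and secondary cessation outcomes alike, a difference in proportions with a 95% confidence interval, a chi-squared p-value, and an odds ratio with its interval.

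**The concern.** The classification rule is written in the plural and excludes neither time point. At six months it fits, because a cotinine sample is requested from everyone who reports abstinence. At one week nobody can satisfy it, because nothing is collected that could verify the report. Read as it stands, the analysis section reclassifies every one-week self-reported quitter as a smoker.

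Two things are at stake. One of only two secondary cessation outcomes has an analysis rule that cannot be carried out and that conflicts with the outcome's definition. In addition, this sentence is the only text that says how one-week non-responders are to be counted, since the definition's loss-to-follow-up rule is given for six months alone. If the sentence is set aside for one week, the handling of missing one-week data goes with it.

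**Working it through.** **Denominators, from the plan's own figures.** The Sample size section gives 35% versus 49%, two-sided 5%, 80% power, 200 per arm followed up, 85% follow-up and 470 randomised.

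- Required n per arm = [1.96 × √(2 × 0.42 × 0.58) + 0.8416 × √(0.35 × 0.65 + 0.49 × 0.51)]² / 0.14² = (1.368 + 0.582)² / 0.0196 ≈ 194. With 200 per arm the power is 81.2%, so the plan's figure reproduces.
- 400 / 0.85 = 470.6, against the stated 470. With 1:1 allocation that is 235 per arm.

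The article states no rate or power for the one-week outcome, so there is no plan figure to reproduce for it.

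**The texts side by side.**

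| | One week (call 3) | Six months (call 4) |
|---|---|---|
| Source of outcome | Telephone self-report | Telephone self-report plus postal saliva |
| Biochemical verification | None described | Cotinine |
| Lost to follow-up (Outcomes section) | Not stated | Counted as smokers |
| Rule in Statistical analysis | Smoker unless verified | Smoker unless verified |

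The saliva collected by mouthwash in the DNA arm cannot fill the gap. It is for NOD2 genotyping, it is taken before the results booklet is sent, and it is collected in one arm only.

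**The rule applied literally at one week.**

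- Abstainers: 0/235 versus 0/235, whatever participants report.
- Difference: 0/235 − 0/235 = 0.
- Chi-squared: the expected number of abstainers per arm is 0 × 235 / 470 = 0. The statistic divides by that zero and cannot be computed.
- Odds ratio: (0 × 235) / (0 × 235) = 0/0, undefined.

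**The rule with verification limited to six months.** One-week rates have to be assumed. With self-report and non-responders counted as smokers (235 per arm):

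| Assumed rates | Counts | Difference, points (95% CI) | Odds ratio | p |
|---|---|---|---|---|
| 5% vs 10% | 12 vs 24 | 5.1 (0.3 to 9.9) | 2.11 | 0.037 |
| 10% vs 15% | 24 vs 35 | 4.7 (−1.3 to 10.7) | 1.54 | 0.13 |
| 10% vs 20% | 24 vs 47 | 9.8 (3.4 to 16.2) | 2.20 | 0.003 |

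These rows show only that the comparison becomes estimable. They do not predict a result.

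**The part left open.** Suppose 200 per arm responded at call 3; this borrows the 85% follow-up rate, which the article does not state for that call. The same 24 and 47 reports then give (47 − 24)/200 = 11.5 points among respondents, against (47 − 24)/235 = 9.8 points with non-responders as smokers. The choice of denominator changes the estimate, and would matter more if response differed between arms.

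**The case against.** The strongest reply is that specific text governs general text. The one-week outcome has its own definition as self-report, repeated under Telephone call 3, while the cotinine sample and its cut-off sit only with the six-month outcome. The analysis sentence presents its rule as a common convention, so it reads as shorthand for missing-equals-smoker and not as a redefinition. The authors most likely meant verification to apply at six months only. A separate analysis plan, not shown here, is to precede analysis and may already split the rule.

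Much of this stands. A reader might infer that the one-week outcome is certain to be reported as 0% in both arms, or that it is lost. The documents do not support that: it would happen only if an analyst discarded the call 3 answers that the Procedure and Outcomes sections say are collected. A reader might also infer that any self-report analysis at one week would be defined after the fact. That is not supported either, because self-report is the published definition.

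What does not fall away is the conflict itself. The likely intention is nowhere written, and the only stated exception is for the primary outcome. Nor is this detail simply left to the analysis plan: the article fixes a rule, and for one named outcome that rule does not work. An analysis plan that followed it would inherit the fault, and one that departed from it would contradict the published text.

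**Conclusion.** The point holds as an inconsistency in the analysis rule for one secondary outcome. Under the literal wording there can be no one-week abstainers in either arm, and two of the planned statistics cannot be computed. Under the likely intended reading the outcome is analysable as self-report, but the article then has no explicit rule for one-week non-responders.

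The conclusion rests on the texts alone. The only assumptions are the illustrative one-week rates and the call 3 response used above, and it does not depend on them. The primary outcome has its own missing-data rule, Hypotheses I to III concern quit attempts, and the six-month outcome fits the verification rule, so none of these is touched. Severity is minor to moderate: worth correcting before analysis, with no threat to the trial's main conclusion.

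**What to change.** Restrict the verification condition in the Statistical analysis section to the six-month outcome, and add the one-week rule. Suggested content:

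- **Six months:** abstinent only if biochemically verified. Non-responders, those who report abstinence but return no sample, and those at or above the cotinine limit are counted as smokers.
- **One week:** self-reported seven-day abstinence at Telephone call 3. Non-responders are counted as smokers, and the result is labelled self-reported and unverified wherever it appears.

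The label is warranted because participants know their arm, and caller blinding is stated for Telephone call 4 but not for call 3.

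The cost is a sentence or two in the analysis section or the analysis plan, settled before the data are analysed. No new data, contacts or participants are needed. The one drawback is that the one-week result is openly presented as unverified, which is what it is.

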### Outcomes

#### Primary outcome

The primary outcome, assessed six months after the intervention, is making one or more quit attempts of 24 hours or longer in the six months following assessment of CD risk. This end point is a reliable predictor of eventual cessation [20].

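### The missing = no quit attempt re-analysis codes as failures lost participants whose call 3 record already shows a qualifying stop

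*Protocol article*

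**What the plan says.** The Protocol article (Outcomes, Primary outcome) defines the primary outcome as "making one or more quit attempts of 24 hours or longer in the six months following assessment of CD risk". Under Procedure, it is ascertained at Telephone call 4: "This will take place six months after the second telephone call to assess the primary endpoint". The Statistical analysis section treats it as the proportion "reporting having made one or more quit attempts of 24 hours or more in the preceding six months".

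An earlier contact also yields smoking data. Call 2 comes after the risk information: "Following receipt of the results booklet, the research counsellor will telephone the participant". At call 3, a team member who did not deliver the intervention "will assess self-reported seven-day smoking cessation approximately one week after telephone call 2 has taken place". The secondary outcome drawn from this call is described as follows: "Self-reported smoking cessation will be assessed at one week following receipt of the CD risk assessment".

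The Statistical analysis section gives two rules for a missing primary outcome. The main analysis is complete case: "for the primary outcome, those missing this outcome will primarily be treated as missing from the analysis". The second rule is a re-analysis: "the primary difference in proportions will be re-assessed assuming that missing data is imputed as no quit attempt". The section also says that missingness will be compared between arms. Nothing in the article lets a call 3 record count towards the primary outcome.

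**The concern.** The outcome is cumulative. One qualifying stop settles it as yes, and later relapse or loss to follow-up cannot undo that. A participant who reports seven days without smoking at call 3 has normally met it by then. If that participant is lost before call 4, the flat imputation records no quit attempt. For most lost participants this is a pessimistic assumption about something unknown. For this participant it contradicts something the trial has observed.

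The imputation is the only re-analysis of the primary difference for missing data that the article describes. Miscoding known successes lowers the imputed quit-attempt rates in both arms. It also distorts the imputed difference if such participants are more common in one arm. The trial's main hypothesis predicts more quit attempts in the DNA arm, so an imbalance is possible, but the article gives no figure for it.

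**Working it through.** **1. Does a call 3 positive imply the primary outcome?** Call 2 follows the booklet and call 3 comes about a week after call 2, so the seven days before call 3 fall after the risk information and within the six months. Seven days is 168 hours, well over 24. The article allows up to 5 cigarettes in seven days for validated abstinence at six months. If that tolerance were also applied at call 3, 5 cigarettes would split 168 hours into at most 6 gaps, so the longest gap is at least 168/6 = 28 hours. The implication still holds.

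**2. Reproducing the plan's figures.** Inputs (Abstract; Sample size; Statistical analysis): 470 randomised 1:1, 85% followed up, 200 per arm analysed, 35% against 49%, two-sided 5%.

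- Power = Φ{[0.14 × √200 − 1.96 × √(2 × 0.42 × 0.58)] / √(0.35 × 0.65 + 0.49 × 0.51)} = Φ(0.885) = 81.2%, against 80% stated.
- 400/0.85 = 471, against 470 stated.

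Both agree with the article.

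**3. Numbers lost.** 470/2 = 235 per arm; 235 − 200 = 35 lost per arm, about 70 in all.

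**4. The re-analysis as written.** At the planned rates, 70/200 and 98/200 report an attempt, a complete-case difference of 14.0 points. With all 35 lost per arm set to no attempt: 70/235 = 29.8% and 98/235 = 41.7%. The difference is 28/235 = 11.9 points.

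**5. The re-analysis with call 3 positives kept.** Let a be the share of all lost participants in an arm who have a call 3 record of abstinence. The article does not give a, so it is an assumption and is varied. Anyone lost before call 3 contributes nothing to it. The rate becomes (attempts reported + 35a)/235.

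| a, non-DNA | a, DNA | Non-DNA rate | DNA rate | Difference (points) |
|---|---|---|---|---|
| 0% (as written) | 0% | 29.8% | 41.7% | 11.9 |
| 5% | 5% | 30.5% | 42.4% | 11.9 |
| 10% | 10% | 31.3% | 43.2% | 11.9 |
| 20% | 20% | 32.8% | 44.7% | 11.9 |
| 5% | 15% | 30.5% | 43.9% | 13.4 |
| 5% | 25% | 30.5% | 45.4% | 14.9 |
| 15% | 5% | 32.0% | 42.4% | 10.4 |

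Equal shares raise both rates by 1.75/235 = 0.7 to 7/235 = 3.0 points and leave the difference alone. A 10-point imbalance moves the difference by 3.5/235 = 1.5 points, and a 20-point imbalance by 7/235 = 3.0 points. The sign follows the direction of the imbalance.

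**6. Could call 3 positives simply be added to the complete-case analysis?** Only known successes among the lost would then enter, and the rest would stay out. With 5% in each arm the rates rise to 71.75/201.75 = 35.6% and 99.75/201.75 = 49.4%. With 20% in each they rise to 77/207 = 37.2% and 105/207 = 50.7%. With 10% in the non-DNA arm and 20% in the DNA arm they are 73.5/203.5 = 36.1% and 105/207 = 50.7%, a difference of 14.6 points against 14.0. Entry to the analysis would depend on the outcome.

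**The case against.** Using call 4 alone is a defensible choice. Its caller is blind to allocation, and everyone is asked the same question about the same period. The call 3 caller need only not have delivered the intervention, and the question concerns seven-day status, not an attempt of 24 hours. Because the primary outcome is an unverified self-report, one blinded source has real value. This stands as a reason to leave the primary analysis as it is and to keep the flat imputation alongside any revised version.

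A call 3 abstainer need not have made an attempt after the risk information. The booklet is posted about six weeks after initial contact, and someone who stopped in that interval could be abstinent at call 3 without starting an attempt in the window. The Abstract's wording, stopping for 24 hours or longer, would still cover that person; the Primary outcome section arguably would not. This narrows the group but does not empty it.

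Deriving an outcome from several contacts is often left to the SAP, which is not shown and could add such a rule. However, the article states both missing-data rules outright, and in this section it defers only the mutation-status sensitivity analysis to the SAP.

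The affected group must stop almost at once and then be lost, so it is probably small. The planned comparison of missingness between arms gives some protection against differential loss, although it does not show which lost participants had already stopped.

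**Conclusion.** The point holds for the imputed re-analysis. As written, the rule codes as failures some participants whose call 3 record shows otherwise. The number is unknown. On assumed shares of 5% to 20% it is about 2 to 7 of the 35 lost per arm. That lowers both imputed rates by 0.7 to 3.0 points and does not change the difference unless the shares differ between arms. Each 10 points of imbalance is worth about 1.5 points.

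A reader might infer three stronger conclusions, and the document does not support them.

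- **That the complete-case primary analysis is at fault for discarding known successes.** It drops lost successes and lost failures alike, and bringing back only the successes would introduce selection on outcome.
- **That the re-analysis is pulled towards no difference.** This requires more lost call 3 abstainers in the DNA arm, which is an assumption. The reverse imbalance moves the result the other way, to 10.4 points in the example.
- **That the re-analysis is useless as a robustness check.** It is a labelled secondary analysis. Where it errs towards no difference, an effect that survives it is still informative.

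This is a small correction worth making because it costs almost nothing and replaces a known error with recorded data.

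**What to change.** In the missing = no quit attempt re-analysis, count a participant recorded as seven-day abstinent at call 3 as having made a quit attempt. Where it is known, restrict this to those still smoking when the booklet arrived. Impute no quit attempt only for the remaining lost participants. Report the flat imputation beside it for comparison.

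Leave the complete-case primary analysis as it is, and do not add call 3 positives to it on their own. If call 3 data are to inform a further analysis, handle all lost participants jointly, for example by multiple imputation with call 3 status in the model.

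The cost is one sentence in the Statistical analysis section or the SAP, using data already planned for collection. The downside is that a few outcomes in this re-analysis will rest on a call 3 self-report whose caller is not stated to be blind to allocation. Keeping the flat version lets readers see how much depends on them.

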### Sample size

#### (a) Hypothesis I

The initial sample size estimate comprised 540 smokers who were FDRs of probands with Crohn's disease. 270 would be cluster randomised by family to DNA testing and 270 to the non-DNA arm. Allowing for 20% dropout we expected to follow-up 215 per arm. With this sample size, and allowing for clustering, there was 80% power to detect an odds ratio (OR) of 1.75 for likelihood of engaging in a quit attempt between randomised arms using a two-sided test at the 5% level of significance. In a general population sample without presentation of risk information 29% reported a quit attempt by six-month recall [25]. On this basis we have estimated that the proportion reporting having made one or more quit attempts of 24 hours or more in the preceding six months would be 35% in the non-DNA arm, enabling detection of 49% or higher in the DNA testing intervention arm (OR = 1.75). In order to allow for clustering effects by family the sample size was increased by a design effect of 8%. This was based on a mean cluster size of 1.13 from the pilot study [18] and an allowance that the intracluster correlation (ICC) could be as high as 0.6 based on observing a range of ICCs between 0.3 and 0.87 for behavioural outcomes clustered at the household level [26].

To check the assumptions underlying the sample size calculation, an interim analysis including the first 266 (50%) participants was conducted. This revealed a higher completion rate (87%), confirmed the cluster size (mean cluster size 1.14) and identified the ICC to be zero. The trial steering committee supported a revised sample size calculation based on a follow-up rate of 85% and without the need to account for clustering in the analysis. This meant that without loss of power for primary or secondary outcomes we could follow up 200 per arm, requiring recruitment of only 470 randomised participants.

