#### (b) Method

Each participant will be cluster randomised by family to one of the two arms, with allocation on a 1:1 basis. The allocation method will be blocked randomisation with the randomisation sequence prepared by the trial statistician.

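### The one imputation stated for missing primary outcomes sets every lost participant, in both arms, to no quit attempt; it cannot test outcomes among the lost that differ by arm, and it picks up a retention artefact when loss is unequal

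*Protocol article*

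**What the plan says.** The Statistical analysis section handles the primary outcome (one or more quit attempts of at least 24 hours in six months) in three steps.

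- Main analysis on complete cases: "those missing this outcome will primarily be treated as missing from the analysis".
- A comparison of missing status between the arms.
- One re-analysis with a filled-in value: "the primary difference in proportions will be re-assessed assuming that missing data is imputed as no quit attempt". The value is the same in both arms.

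For the secondary cessation outcomes the section uses a different rule: everyone counts as a smoker unless biochemically verified as abstinent. It mentions a later statistical analysis plan, but only in connection with the sensitivity analysis on mutation status.

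Sample size, (a) Hypothesis I, gives the attempt rates behind the design: "In a general population sample without presentation of risk information 29% reported a quit attempt by six-month recall", with 35% expected in the non-DNA arm and 49% as the detectable rate in the DNA arm. Planned follow-up is 85% of 470 randomised, or 200 per arm.

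**The concern.** A sensitivity analysis for missing data should ask whether departures from the main analysis's assumption could change the conclusion. For Hypothesis I the damaging departure is that lost DNA-arm participants attempted less often than lost non-DNA participants. Giving both arms the same value cannot represent that.

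The chosen value is also an awkward one. Counting the lost as smokers is customary for abstinence. A 24-hour attempt is a much weaker event, and none of the attempt rates that the protocol quotes is near 0%.

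Two errors could follow. With similar loss in the arms, the re-analysis will nearly always agree with the main result and may be read as support that it does not give. With different loss, it will move because of retention alone, in either direction. About 15% of outcomes are expected to be missing. Only the DNA arm has to return a sample before results are issued, so unequal loss is possible, though the protocol gives no figures by arm.

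**Working it through.** **Inputs from the protocol.** 470 randomised 1:1, so 235 per arm; 200 per arm followed up, so 35 lost per arm; 35% v 49%; two-sided 5% level; 29% from the general population sample.

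**Assumed, not in the protocol.** The attempt rates among the lost, and any split of loss by arm. Where the lost are said to behave like the rest of their arm, that too is an assumption.

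**The plan's own figure.** The pooled two-proportion test needs 194 per arm for 35% v 49% at 80% power; 200 per arm gives 81.2%. Inflating, 400/0.85 = 471 against 470 stated. The stated sample size is reproduced.

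**Step 1: equal loss.** Test: z = (p1 - p0) / sqrt[p(1 - p)(1/n1 + 1/n0)], with p the pooled proportion.

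- Complete cases: 98/200 v 70/200, 14.0 points, z = 2.84, p = 0.005.
- Stated re-analysis: 98/235 v 70/235, 11.9 points, z = 2.69, p = 0.007.
- 29% imputed in both arms adds 0.29 x 35 = 10.15 to each numerator: again 11.9 points, z = 2.64, p = 0.008.

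Any common value m gives (98 + 35m)/235 - (70 + 35m)/235 = 28/235 = 11.9 points. At equal loss the choice between 0% and 29% therefore does not affect the estimate.

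**Step 2: unequal loss, no true effect.** With attempt rate q in both arms, and the lost behaving like the rest of their arm, imputing m shifts the difference by (q - m) x (loss non-DNA - loss DNA). With q = 0.35:

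| Lost, DNA v non-DNA | Shift, m = 0 | Shift, m = 0.29 | Rejection rate, m = 0 |
|---|---|---|---|
| 15% v 15% | 0 | 0 | 5% |
| 18% v 12% | 0.35 x (-0.06) = -2.1 points | 0.06 x (-0.06) = -0.4 | about 8% |
| 20% v 10% | 0.35 x (-0.10) = -3.5 points | 0.06 x (-0.10) = -0.6 | about 13% |

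The rejection rates come from simulation (200,000 trials or more, 235 per arm, binomial retention).

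**Step 3: unequal loss, true 49% v 35%.** By the same simulation, complete cases are significant in 81% of trials throughout. The stated re-analysis is significant in 77% (15% v 15% lost), 56% (18% v 12%), 41% (20% v 10%) and 91% (12% v 18%).

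**Step 4: does the missing-status comparison cover this?** It reaches p < 0.05 in about 45% of trials at 18% v 12% lost. On expected counts, 80% v 90% retained gives p = 0.002 and 82% v 88% gives p = 0.07. It looks at rates of loss and says nothing about outcomes among the lost.

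**Step 5: arm-specific outcomes at equal loss.** Observed 98/200 v 70/200, 35 lost per arm.

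| Attempt rate among lost, DNA / non-DNA | Difference (points) | p |
|---|---|---|
| 0% / 0% (stated) | 11.9 | 0.007 |
| 20% / 35% | 9.7 | 0.032 |
| 10% / 35% | 8.2 | 0.069 |
| 0% / 23% (0 v 8 of 35) | 8.5 | 0.057 |
| 0% / 29% | 7.6 | 0.090 |

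With no attempts among the lost DNA-arm participants, 7 of 35 among the lost non-DNA participants leaves p = 0.045, and 8 of 35 tips it. The stated re-analysis gives p = 0.007 whichever row is true.

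**The case against.** The case for the plan is substantial, and several parts of it stand.

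- A reader might infer that zero imputation is the only check on missingness. It is not: the same sentence compares missing status between arms, so a large difference in loss would be seen. It is the only imputation stated.
- A reader might infer that the re-analysis mainly measures retention. It does not. At 80% v 90% retained with 49% v 35%, the re-analysed 7.7 points consist of 0.85 x 14 = 11.9 from the effect and 0.42 x (-0.10) = -4.2 from retention. Retention dominates only the movement away from complete cases, and only when loss is unequal.
- The 29% is a general-population figure without risk information, not a rate for participants lost from this trial. The protocol gives no such rate, and 0% is a legitimate boundary value.
- The simulations let the lost behave like the rest of their arm, which makes complete cases unbiased by construction. They show how the re-analysis responds to retention, not that complete cases are safe. The unequal loss rates are illustrative; the interim 87% completion is not split by arm.
- Tipping needs more than a small departure. At 20%/35% among the lost the result stays significant, and the 0%/23% case puts the lost DNA arm 49 points below its observed rate.
- The analysis plan is not shown and may add further analyses. Their absence from the article is not a fault.

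What remains is a method that the protocol states, not a detail that it leaves open. One common value cannot examine arm-specific outcomes among the lost, and the missing-status comparison does not fill that gap.

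**Conclusion.** The point holds as a cheap improvement to a stated method. It is not an error that invalidates the primary analysis, and complete cases can remain primary.

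At equal loss the stated re-analysis is close to uninformative: it scales the difference by 200/235 and hardly moves z. At unequal loss it carries a retention term of about 2 to 3.5 points under the assumed loss splits, with false rejection of about 8% to 13% in place of 5%. The pattern that would threaten Hypothesis I, different attempt rates among the lost in the two arms, is not examined by any analysis stated in the protocol.

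The sizes rest on the design rates of 35% and 49%, on 35 lost per arm for the tipping cases, and on the assumed loss splits for the retention figures. The documents do not show that loss will be unequal or that the lost will differ by arm. They show only that the stated re-analysis could not reveal the second.

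**What to change.** In the Statistical analysis section, keep complete cases as primary and keep the comparison of missing status. Replace the single re-analysis with an arm-specific tipping-point grid:

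- let the attempt rate among the lost vary separately in each arm, for example from 0% to 60%;
- show 0%/0% as one corner, so that the present re-analysis is retained, and mark 29%/29% as a reference point;
- report the difference in proportions at each point, and the pairs at which the two-sided p-value crosses 0.05.

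Multiple imputation by arm, using data from telephone calls 1 and 3, is an optional addition.

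The cost is one paragraph in the plan and a little programming, with no new data, participants or staff. The drawback is that readers get a table of results in place of one extra p-value.
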